### **Statistical Analyses**

We will perform chi-squared tests to compare uptake at various non-zero prices to uptake at the price of zero (i.e. free distribution). We will also use regression analyses to estimate the elasticity (i.e. price-sensitivity) of the demand for self-tests. We will estimate unadjusted regression models as well as adjusted regression modes that include covariates such as individual characteristics, particularly those that differ between study groups. The subgroup analyses will be performed by comparison of means and by regression analyses that use interaction terms. Robust standard errors that allow for clustering of standard errors within communities and households will be reported for all regressions.

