## **STUDY DESIGN**

### **Overview of Study Design**

We will conduct a rigorous field experiment in urban and rural communities near Harare, Zimbabwe, to estimate individuals’ demand for oral fluid-based and blood-based HIV self-tests. About 4,000 adults will be randomly selected in study communities, administered a short questionnaire, and given referral vouchers that will enable them to obtain HIV self-tests at randomly allocated prices and distribution sites. All participants will be given a brief description of HIVST during the time of enrollment. In addition, all self-tests will include easy-to-use instructions that have been carefully developed based on prior studies in Zimbabwe. A link to an instructional video may also be provided to those who have access to a

phone and express interest in receiving a link to the video. Uptake of HIVST will be monitored at the distribution sites, where the vouchers will be collected in exchange for self-tests; the voucher numbers will enable us to link HIVST uptake to individual participants.

In a subsequent study with additional funding, we will also seek to determine the long-term implications of offering self-tests at very low prices initially; specifically we will assess whether free distribution initially suppresses individuals' willingness to pay for self-tests in the future. Roughly 12 months after the initial voucher offer, participants who provided a mobile phone number they can access within their household will be contacted via phone-based text messages and offered the same HIV self-tests again at one common non-zero price. The purchases at 12 months will once again be monitored and linked to participants via a unique identifier that is included in the text messages.

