### **Consent and Enrollment Processes**

Households in the study locations will be randomly selected using a door-to-door strategy. In each household, research assistants will randomly select one eligible individual and invite them to participate in the study, following a standard randomization protocol. Research assistants will review the informed consent form with eligible individuals. Those who provide consent will be enrolled into the study and administered a brief baseline questionnaire.

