### **Randomization Procedures**

After completing the baseline questionnaire, participants will be given general information about HIVST and then assigned to one of the experimental arms based on computer-generated randomization. Participants will be given one referral voucher that offers a self-test kit at the random price and distribution site determined on the tablet computer. The vouchers will be valid for one month after the enrollment date – meaning that individuals will have up to one month to decide whether to

purchase/obtain self-tests. Each voucher can be used to redeem one self-test kit at the specified price and distribution site. The other household members above 16 years of age will also be offered one voucher per person. Vouchers for the same household will have the same price, distributor, and promotion messages.

Research assistants will clearly explain to participants how they can redeem the voucher. The out-of-pocket price that participants must pay for self-tests will be written clearly on the voucher and will range from \$0 (free/fully subsidized) to up to \$3. Up to five different prices will be used in the study and all of the prices will be below the current full market value of self-tests, meaning that all participants will be offered self-tests at a discounted price. Each voucher will have a unique identifier to determine whether the participants obtained self-tests within one month at the distribution sites. Computer-generated block randomization will be used to determine the sequence of prices & distribution sites on vouchers.

Distribution channels at which the self-tests will be sold or offered will be determined in consultation with PSI/Z and CeSHHAR staff. In rural communities, the distribution channels may include community health workers and retail shops to ensure access for all participants. In urban areas, the distribution channels may include pharmacies and local clinics.

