### **Outcomes**

The primary outcome will be the proportion of individuals that purchased or obtained at least one HIV self-test in each of the study groups. This will enable us to estimate the proportion of individuals who would buy self-tests at various prices, and the proportion of individuals who would buy self-tests at various combinations of price and distribution site.

In addition, we will examine how the likelihood of purchase vary by price and distribution site in key segments of the population, including individuals who have and have not tested for HIV in the past, individuals with low and high risk of HIV infection based on self-reported sexual behavior, and individuals with low and high income.

Finally, with additional funding in the future, we will compare the proportions of individuals who purchase HIV self-tests at the common price offered at about 12 months based on whether they initially received a partially or fully subsidized price. This will enable us to explore whether individuals' demand for HIV self-tests over the long term is contingent on the price that is initially offered to them.

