### **Sample Size and Power Calculation**

The power analysis for this study focused on the primary outcome that compares the proportion of individuals who purchased at least one HIV self-test with vouchers at low vs. high price points. The power calculations allow for analyses to be stratified by rural vs. urban clusters. Assuming 15% of individuals would make a purchase when offered the highest price, the sample size required to detect a 10-percentage-point increase in the percentage of individuals who purchase at lower prices will be 270 per group (80% power and a type I error of 0.05). Thus, a sample size of about 2,000 adults in rural areas and 2,000 adults in urban areas (for a total sample of about 4,000 adults) will allow for five different price points to be used in each area.

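### The protocol leaves open whether other household members' redemptions count; if they do, the plain chi-squared price tests give p-values that are too small

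*Protocol*

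**What the plan says.** **Assignment.** Under Randomization Procedures, the enrolled participant receives one voucher at a random price and site. Then: "The other household members above 16 years of age will also be offered one voucher per person". And: "Vouchers for the same household will have the same price, distributor, and promotion messages". Price therefore varies between households and not within them.

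**Enrolment.** Under Consent and Enrollment Processes: "In each household, research assistants will randomly select one eligible individual and invite them to participate in the study". Consent and the baseline questionnaire are described for that person only. The Overview of Study Design adds that "the voucher numbers will enable us to link HIVST uptake to individual participants".

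**Outcome.** Under Outcomes: "The primary outcome will be the proportion of individuals that purchased or obtained at least one HIV self-test in each of the study groups". The sentence neither restricts the count to enrolled participants nor extends it to other voucher holders.

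**Tests.** Under Statistical Analyses, the comparison of each non-zero price with free distribution is by chi-squared test: "We will perform chi-squared tests to compare uptake at various non-zero prices to uptake at the price of zero (i.e. free distribution". No adjustment is named. The section ends: "Robust standard errors that allow for clustering of standard errors within communities and households will be reported for all regressions".

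**The concern.** One section treats the same outcome in two ways. The regressions allow for correlation within households; the chi-squared tests do not. Household clustering has work to do only if more than one person per household is in the data. If that is intended, the chi-squared tests count people who share a price, a site and possibly a trip as independent observations, and their p-values are too small whenever redemption is positively correlated within households. If it is not intended, the household clustering is redundant.

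The protocol does not settle which applies. The choice bears on the trial's central question, whether charging reduces uptake relative to free distribution, and it could otherwise be made after the redemption data are seen. There is a second consequence. The baseline questionnaire is described only for enrolled participants, so adjusted and subgroup models can cover only them. Chi-squared tests on all voucher holders would then rest on a different population.

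**Working it through.** **Step 1: the plan's own sample size.** Inputs from Sample Size and Power Calculation: 15% uptake at the highest price, a 10-point increase (so 25%), 80% power, alpha 0.05. Two-sided testing is assumed, as the sidedness is not stated.

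n = [1.960·√(2·0.20·0.80) + 0.8416·√(0.15·0.85 + 0.25·0.75)]² / 0.10² = (1.1087 + 0.4724)² / 0.01 ≈ 250.

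With continuity correction: (250/4)·[1 + √(1 + 4/(250·0.10))]² ≈ 270.

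This matches the stated 270 per group. The figure is for independent individuals, that is, a design effect of 1.

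**Step 2: numbers available.** 2,000 per area over five prices is 400 enrolled participants per price per area. Power for 15% versus 25% at 400 per group is 94%.

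**Step 3: error of the plain chi-squared test.** Let m be the analysed persons per household (taken as equal across households) and ICC the correlation of redemption within a household. Neither is in the documents, so m = 2 to 3 and ICC = 0.1 to 0.5 are assumed ranges.

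DE = 1 + (m − 1)·ICC; true alpha = 2·[1 − Φ(1.96/√DE)].

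| m | ICC | DE | True alpha, formula | True alpha, simulated |
|---|---|---|---|---|
| 1 | any | 1.0 | 0.050 | not needed |
| 2 | 0.1 | 1.1 | 0.062 | 0.061 |
| 2 | 0.3 | 1.3 | 0.086 | 0.084 |
| 2 | 0.5 | 1.5 | 0.110 | 0.116 |
| 3 | 0.1 | 1.2 | 0.074 | 0.071 |
| 3 | 0.3 | 1.6 | 0.121 | 0.130 |
| 3 | 0.5 | 2.0 | 0.166 | 0.167 |

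The simulation drew beta-binomial households, about 400 persons per group, 20% uptake in both groups, 8,000 runs per row. Over the same range a nominal p of 0.01 corresponds to a correct p of about 0.014 to 0.069. Larger households go further: m = 4 with ICC 0.5 gives DE 2.5 and a true alpha of 0.215.

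**Step 4: does power suffer?** If other members are added to the 400 index participants, the effective number per group is 400·m / [1 + (m − 1)·ICC]. At m = 3 and ICC 0.5 this is 1,200/2.0 = 600; at m = 2 and ICC 0.5 it is 800/1.5 ≈ 533. With equal household sizes it does not fall below 400 for any ICC up to 1.

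**The case against.** The strongest reply is that the protocol, read as a whole, describes one analysed person per household. One person is selected, consents and answers the questionnaire; uptake is linked to participants; and the trial is sized on about 4,000 adults with a design effect of 1, which is correct for that design. Household-clustered errors with one person per household reduce to ordinary robust errors and do no harm. The unadjusted regressions could also test the same price contrasts validly on either reading. Finally, the definition of the analysis set may sit in a statistical analysis plan that is not shown.

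Most of this stands, and it rules out three stronger readings that a reader might infer:

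- **That the p-values are too small as planned.** Nothing says that other members enter the chi-squared tests. With one person per household the level is 5%.
- **That the sample size wrongly omits a design effect.** None is needed for one person per household, and step 4 shows that adding other members to the index participants does not lower power under a clustered test with equal household sizes.
- **That the chi-squared tests are the declared primary analysis.** They are listed first and are the only test named specifically for each price against free, but the protocol does not label them primary.

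The reply does not remove the inconsistency. The protocol goes beyond leaving a detail open: it names the test, recognises household clustering, and applies it to only one of two analyses of the same outcome.

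**Conclusion.** The concern holds conditionally. The protocol does not fix whether other household members' redemptions count towards the primary outcome, and its stated chi-squared rule is valid on only one of the two readings. With the enrolled person alone, true alpha is 0.050. With other voucher holders included and positive within-household correlation, it is about 0.06 to 0.17 for 2 to 3 persons per household and ICC 0.1 to 0.5. That range rests wholly on assumed household size and ICC. Strong sharing of redemption within households is plausible, but the protocol does not document it. A reader might also infer that the unadjusted and adjusted analyses will use different populations; this follows only if other members are counted, and the protocol does not say that they are.

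**What to change.** State in Outcomes and Statistical Analyses that the primary analysis set is the roughly 4,000 enrolled index participants, one per household, and that it applies to the chi-squared tests and to the unadjusted and adjusted regressions. Report other members' redemptions only as a secondary outcome, for example kits redeemed per household. Wherever more than one person per household enters a comparison, replace the plain chi-squared test with a Rao-Scott test or with the unadjusted regression using household-clustered errors. Leave the 270 per group as it is.

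The cost is a few sentences. Where other members are included, intervals become wider than unclustered ones by a factor of √DE, from √1.1 ≈ 1.05 to √2.0 ≈ 1.41 over the assumed range, which is their correct width. The index-only primary analysis keeps about 94% power at 400 per price per area under the plan's own assumptions.

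### Price is block-randomised jointly with distribution site, and channels are nested in area, but the stated tests and regressions name neither area nor channel as a stratum or model term

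*Protocol*

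**What the plan says.** Three parts of the protocol bear on this.

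- **Allocation (Randomization Procedures).** Price and site are assigned in one step: "Computer-generated block randomization will be used to determine the sequence of prices & distribution sites on vouchers". The candidate channels differ by area. For the rural area: "In rural communities, the distribution channels may include community health workers and retail shops to ensure access for all participants". The urban list has clinics and pharmacies instead. No stratification factor is named.
- **Sizing (Sample Size and Power Calculation).** About 2,000 adults are planned in each area, a number that "will allow for five different price points to be used in each area". The section adds: "The power calculations allow for analyses to be stratified by rural vs. urban clusters".
- **Analysis (Statistical Analyses).** The price comparison is a chi-squared test: "We will perform chi-squared tests to compare uptake at various non-zero prices to uptake at the price of zero (i.e. free distribution"). For the models: "We will estimate unadjusted regression models as well as adjusted regression modes that include covariates such as individual characteristics", with emphasis on characteristics that differ between study groups. Standard errors clustered on community and household are promised for the regressions only. Neither area nor channel appears as a stratum or a covariate.

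**The concern.** Area and channel are part of how vouchers are assigned and may well be related to uptake. When such a factor is balanced across prices by design, leaving it out does not bias the price contrast. It does leave the variation between strata in the error term, so the test is less precise than the design allows.

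The covariate rule makes this more than silence. It favours individual characteristics that look imbalanced. Area and channel are not individual characteristics, and balanced allocation makes them look alike across prices, so a reader following the rule would tend to omit them. The sizing by area and the stated test also do not match: the sample is justified by rural and urban analyses that the analysis section never specifies.

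**Working it through.** **Inputs from the protocol.** Uptake of 15% at the highest price and 25% at a lower one; 80% power; type I error 0.05; 270 per group. About 2,000 adults and five prices per area give 2,000 / 5 = 400 per price per area if allocation is equal (assumed, not stated).

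**Reproducing the 270.** Two-sided test, pooled null variance, mean uptake 0.20:

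n0 = [1.96 × √(2 × 0.20 × 0.80) + 0.8416 × √(0.1275 + 0.1875)]² / 0.10² = 249.98, i.e. 250.

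With continuity correction: (n0 / 4) × [1 + √(1 + 4 / (n0 × 0.10))]² = 269.6, i.e. 270. The stated figure is reproduced.

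**Cost of ignoring one balanced two-level factor (area or channel).** Suppose uptake in the two equal strata is p − d and p + d, so the gap is 2d. The mean within-stratum variance is p(1 − p) − d². For 15% versus 25%:

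- Ignoring strata: 0.1275 + 0.1875 = 0.315
- Stratified: 0.315 − 2d²
- SE ratio: √[0.315 / (0.315 − 2d²)]

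| Assumed gap (2d) | Stratified variance | SE ratio |
|---|---|---|
| 6 points | 0.3132 | 1.003 |
| 10 points | 0.3100 | 1.008 |
| 20 points | 0.2950 | 1.033 |
| 30 points | 0.2700 | 1.080 |

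The gaps are assumptions. A 30-point gap is the limit of the range, since it puts the two strata at 0% and 30% around the 15% figure.

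**Power.** Φ(0.10 / SE − 1.96), with SE = √(variance / n):

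| n per group | Ignoring strata | Stratified, 10-point gap | Stratified, 20-point gap |
|---|---|---|---|
| 270 | 83.3% | 83.9% | 85.7% |
| 400 | 94.6% | 94.9% | 95.8% |

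The loss runs from 0.3 points (n = 400, 10-point gap) to 2.3 points (n = 270, 20-point gap). At n = 270 with a 30-point gap, the stratified value is Φ(0.10 / √(0.270 / 270) − 1.96) = Φ(1.202) = 88.5%, a loss of 5.2 points.

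These losses are on the high side if allocation is exactly balanced within strata. The estimate then varies with the smaller SE while the test still uses the larger one. For n = 270 and a 20-point gap, power is Φ[(0.10 − 1.96 × 0.03416) / 0.03305] = 84.1%, so the loss is about 1.5 points rather than 2.3.

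**True size of the unstratified test at 20% uptake in both groups.** 2 × [1 − Φ(1.96 × √(0.16 / (0.16 − d²)))] gives 4.8%, 4.3% and 3.4% for gaps of 10, 20 and 30 points. The test is conservative, not anti-conservative.

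**The case against.** **The protocol never says the tests are pooled.** This stands. Pooling is inferred from the absence of any stratum. The power section foresees rural and urban analyses, and the Outcomes section promises uptake by combination of price and site. If every test were run within area, the area part of the point would fall away and the channel part would remain. Some of this detail could also sit in an analysis plan that is not shown. Against that, the protocol does name a plain test and does state a covariate rule, and that rule points away from the design factors.

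**The loss is small.** This stands too. Much larger figures need extreme strata. Four equal strata at 5/25/35/65% uptake with a 10-point price effect give a variance ratio of 0.798, i.e. an SE about 12% too large (1 / √0.798 = 1.12). Those strata average 32.5%, against the protocol's 15% at the highest price.

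**The direction is not universal.** In a logistic model, adjustment can raise the standard error of the conditional log odds ratio. Vouchers in one household also share a price, so if several members are analysed, a chi-squared test that ignores this clustering has a standard error that is too small. That is a separate issue working in the opposite direction.

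**Confounding of price with area.** A reader might infer this from two statements on the number of prices: "Up to five different prices will be used in the study" and a sample that "will allow for five different price points to be used in each area". The documents do not support it. The two statements fit one common set of up to five prices, and nowhere are the areas given different prices. With a common set and balanced allocation, area does not confound price.

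**Conclusion.** The point holds as one of modest efficiency and specification. The factors that structure the allocation and the sample size are missing from the stated analysis, and the covariate rule would tend to keep them out. The cost on the risk-difference scale is the small one shown above, with a test that stays valid. This rests on assumed gaps between strata, equal allocation of prices within strata, and one independent observation per unit. It does not show that price estimates are biased, or that every standard error in the analysis is too large.

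**What to change.** In Statistical Analyses:

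1. Make each price-versus-free comparison stratified by area × channel, with a Cochran-Mantel-Haenszel test and a stratified risk difference.
2. Include area × channel indicators in the main regressions as fixed design terms, regardless of observed balance. A simple unadjusted model may stay as a secondary description.

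The cost is a change of analysis wording only, with no additional data, participants or fieldwork.

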### **Sample Size and Power Calculation**

The power analysis for this study focused on the primary outcome that compares the proportion of individuals who purchased at least one HIV self-test with vouchers at low vs. high price points. The power calculations allow for analyses to be stratified by rural vs. urban clusters. Assuming 15% of individuals would make a purchase when offered the highest price, the sample size required to detect a 10-percentage-point increase in the percentage of individuals who purchase at lower prices will be 270 per group (80% power and a type I error of 0.05). Thus, a sample size of about 2,000 adults in rural areas and 2,000 adults in urban areas (for a total sample of about 4,000 adults) will allow for five different price points to be used in each area.

### **Data Management**

CeSHHAR Zimbabwe will be the data coordinating centre. This unit is headed by an experienced data manager. Data will be stored securely on password-protected servers (for electronic data) and locked cabinets (in the case of consent forms). Deidentified data will be shared with other study team members for analyses.

Questionnaire data will be collected using Audio Computer-Assisted Self-Interview Software (ACASI) on a tablet with headphones attached. Data validity checks will be built into the ACASI platform. In the field, data will be backed up daily onto “cloud storage”. Laptop computers on which any data may be stored will be kept in locked storage at all times. Field teams will download data into a password protected database accessible only to the project data manager and named study personnel, on a central computer. This will be backed up daily. Hard-copy data will be stored in participant files and locked in a file cabinet located in a secure room accessible only to key study personnel. Participants will be asked to provide written informed consent for participation.

